### Study procedures

#### Screening, enrollment, and participant follow-up

Potential participants were approached through the primary school system. At screening, every child provides a fresh stool (about 5 g) sample, which is used to detect the presence of *S. mansoni*. The geohelminths (hookworms, *Ascaris lumbricoides*, and *Trichuris trichiura*) are recorded. A capillary blood sample is taken by fingerprick to estimate hemoglobin and determine the presence of malaria parasites. Every child who tests positive for *S. mansoni* is invited for confirmation of eligibility. Eligible children will be recruited until the sample size is attained. The benefits of treatment for schistosomiasis and the availability of free medical check-ups were explained to potential participants to encourage participation and to ensure that adequate numbers were enrolled. Ineligible children are treated using a single oral dose of PZQ and referred for further treatment if need be.

At enrollment, verbal assent from the child and written informed consent from the parent/guardian are obtained. The study clinician takes a standard baseline medical history and performs a clinical examination, including weight (using a digital weighing scale), height (using a stadiometer), and temperature (using a digital thermometer) measurements. The clinician also assesses the size of the liver and spleen. All this information will be recorded on a paper-based case record form, which the principal investigator reviews to ensure compliance with the study protocol. Children receive study treatment according to the randomization list. Administration of all the study drugs is directly observed by the study nurse. All study drugs are given orally by the study nurse. For each child, the nurse records whether they have received their scheduled treatment, the dose, and reasons for missing treatment. A copy of the treatment sheet with dosing regimens is provided as supplemental material (Additional file 1: Appendix 4).

Children are followed up at weeks 6 and 12 after starting treatment. During the first 3 days after enrollment, they are visited at school or home daily to administer study treatment and complete the adverse events questionnaire. At the week 6 and 12 follow-up visit, the children provide an early morning stool sample, and the study clinician takes a brief medical history, performs a clinical examination, and obtains a fingerprick blood sample for hemoglobin estimation. Participants who do not return for the scheduled follow-up visits are visited at home.

A detailed schedule of the study procedures at different time points is presented in Table 1.

**Table 1 Tab1:** Scheduled visits and procedures

	Enrollment/baseline	Allocation	Intervention (3 days)			Follow-up	
	− D5	D0	D0	D1	D2	Week 6	Week 12

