### Study design

The SCHISTOACT study is designed as a phase III, open-label, five-arm, head-to-head, proof-of-concept, individually randomized, controlled, non-inferiority trial. The participants are randomly allocated (ratio 1:1:1:1:1) individually to one of five treatment groups. At baseline, participants in the control arm receive praziquantel (PZQ, single dose of 40 mg/kg). Those in the intervention arms receive a single dose of praziquantel (40 mg/kg) plus a 3-day course of one of four artemisinin-based combination therapies (4 mg/kg of the artemisinin component, once a day for three consecutive days, as fixed-dose WHO-recommended combination treatment for uncomplicated falciparum malaria). The four artemisinin-based combination therapies (ACTs) that are combined with praziquantel are artesunate plus sulfalene/pyrimethamine, artesunate plus amodiaquine, artesunate plus mefloquine, and dihydroartemisinin-piperaquine. These four ACTs were selected because they are widely available for malaria treatment, co-formulated, for once-daily dosing therapy, have a well-established safety profile and have all been evaluated for treating schistosomiasis with inconclusive results. The 6-week interval between the administration of study treatment and evaluation of primary endpoints has been chosen because it corresponds to the duration of schistosome larval maturation. The participants will be followed up at 6 and 12 weeks. During these follow-up visits, stool samples will be collected, and clinical assessments will be performed. All children will receive a standard dose of praziquantel at the end of the study. The study flow chart is shown in Fig. 1.

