### Adverse events

The study nurse administers all the study drugs. Children will ingest the study drugs with a small amount of water. Before administering the study treatment, all the children are given a light meal (slices of bread and a glass of orange juice) to reduce the study drugs’ nauseating effect and improve drug bioavailability [32]. Participants are observed for 1 h after drug ingestion to ensure retention and to assess for any immediate adverse events. Participants who vomit within 1 h of drug ingestion are re-dosed. Participants with repeated vomiting are withdrawn from the study.

All adverse events are elicited by asking the children about any adverse drug reactions observed after taking the study drugs. The symptoms will be assessed, graded (according to their intensity as perceived by the child) by the study clinician, and recorded on the adverse event form. The adverse events form is administered an hour after study treatment and 24 h later (before the next ACT dose). The following information is recorded on the adverse events form: adverse event description, duration (start and end dates); severity grade (mild, moderate, severe); causality (relationship to the study drugs); action(s) taken; and the outcome. The participants who develop adverse events (AEs) or serious adverse events (SAEs) are treated appropriately and followed up until they return to a normal state of health. The investigator reports any SAE occurring or observed during the follow-up period to the KEMRI Scientific and Ethics Review Unit within 48 h of being aware of the event.

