### Concomitant treatment

According to the national treatment guidelines, all children with helminthic infections are treated with a single dose of 400 mg of albendazole. A list of prohibited or contra-indicated medicines was availed to the study clinicians. Participants are prohibited from taking any non-study drugs during the study. The study clinician evaluated any reports of non-study medications taken to assess for possible drug interactions.

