#### Withdrawal

Participation is voluntary, and participants can withdraw from the study at any time and for any reason without consequences. Participants will be withdrawn from the study due to repeated vomiting or occurrence of SAE. Children with SAEs are followed up until the end of 6 weeks after the last treatment dose. Participants withdrawn from the study due to medical reasons are referred to adequate health facilities for further care. Unless consent is withdrawn, efforts are made to assess these children at the week 6 follow-up schedule.

Valid reasons for study discontinuation include completion of the scheduled follow-up period and exclusion from follow-up. Randomized participants who miss one or more scheduled follow-up visits remain in the study and are followed up as planned. Loss to follow-up is expected to be minimal because all the participant-related study procedures are completed at school and, if necessary, at home. In the unlikely event that a study participant moves away from the study area during the study period, they are considered lost to follow-up and are not included in the efficacy analysis. However, data collected up to the time of withdrawal will remain in the study and be used for analysis of whether or not the participant continues with the follow-up visits. Participants who have been withdrawn from the study are administered a standard dose of praziquantel after the final study visit. No additional participants are recruited to replace those who have withdrawn.

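### The rule giving praziquantel to ineligible children does not except those excluded for praziquantel hypersensitivity

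*Protocol article*

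**What the plan says.** Two parts of the protocol article's Methods bear on this.

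- **Eligibility criteria.** Seven exclusion criteria are listed. One is a past hypersensitivity reaction to any of five named drugs or drug classes, the last of which is praziquantel.
- **Screening, enrollment, and participant follow-up.** Each child whose stool is positive for *S. mansoni* "is invited for confirmation of eligibility". For those who fail that check the article states: "Ineligible children are treated using a single oral dose of PZQ and referred for further treatment if need be".

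The second statement is a positive instruction to dose. It carries no condition on the reason for ineligibility.

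**The concern.** Offering standard treatment to infected children who cannot join the trial is right, and for most reasons for exclusion the rule is sensible. It fails for one reason on the article's own list: a child known to react to praziquantel is kept out of the trial and is then, by the next instruction, given praziquantel. What is at stake is the safety of that child. The cure-rate comparison is not at stake, because such a child is never randomized.

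**Working it through.** No arithmetic decides this point, and there is no plan figure to reproduce. The check sets the instructions side by side and looks for an exception.

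1. **Who reaches the eligibility check.** Children with a positive stool result (Screening, enrollment, and participant follow-up). The group then called ineligible therefore includes infected children who meet an exclusion criterion.
2. **Why they may be excluded.** The seven criteria concern body weight, hemoglobin, *P. falciparum* co-infection, severe malnutrition, convulsions, drug hypersensitivity, and recent antimalarial or anti-schistosomal treatment. Only the hypersensitivity criterion names a past reaction to the drug that the rule then gives, and praziquantel is 1 of the 5 drugs or classes in it.
3. **What the rule directs for them.** One oral dose of praziquantel, whatever the reason for exclusion.
4. **Combining 1 to 3.** A child who is infected and has a known praziquantel reaction is ineligible, and so is to be given praziquantel.
5. **Does anything in the article stop this?**
   - The referral in the same sentence is joined to the dose by 'and', and applies only if needed. It does not replace the dose.
   - Under Concomitant treatment: "A list of prohibited or contra-indicated medicines was availed to the study clinicians". That section concerns non-study medicines taken by participants. It does not say that the list governs the dose for children who were not enrolled.
   - The sections on discontinuation, withdrawal and adverse events apply to enrolled participants, which this child is not.

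   None of these withholds the dose.
6. **How many children.** The article gives no count of children screened, excluded or reporting a reaction to praziquantel. The ratios 1 of 7 and 1 of 5 describe the list, not frequencies, so no number can be derived.
7. **Timing.** Trial status gives the end of recruitment as 30 November 2022, and the article was published on 27 November 2023. From 30 November 2022 to 30 November 2023 is 365 days, so the gap is 365 − 3 = 362 days. Doses for children found ineligible at screening were therefore probably all given before publication.

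**The case against.** The strongest reply is that this is a condensed article. Handling of contraindications is routine clinical detail that the full protocol (version 1.2) or its appendices may contain. The investigators plainly regard praziquantel hypersensitivity as a reason not to give study treatment, since they list it. The dosing sentence can be read as a summary of standard care, and no sensible clinician would dose such a child. Nor do the two sections strictly contradict each other, because the exclusion criterion governs enrolment only.

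Much of this stands. It limits the point to wording and makes actual harm unlikely. It does not remove the point, because the article does more than stay silent: it states a dosing rule whose scope takes in a child whom the same article identifies as hypersensitive. A reader who re-uses the rule would copy it without the exception.

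A reader might go further and infer the same defect in the later praziquantel doses. Under Withdrawal: "Participants will be withdrawn from the study due to repeated vomiting or occurrence of SAE", and then "Participants who have been withdrawn from the study are administered a standard dose of praziquantel after the final study visit"; under Study design: "All children will receive a standard dose of praziquantel at the end of the study". It is tempting to conclude that a child with a praziquantel-related serious adverse event is to be re-exposed, and that the causality record already identifies such a child. The article does not support that as a finding:

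- Withdrawal follows any serious adverse event, whatever its cause, so being withdrawn does not mark praziquantel as unsafe for that child.
- The adverse event form records "causality (relationship to the study drugs"), with nothing to show that causality is assigned drug by drug. In four of the five arms praziquantel and the artemisinin combination both start on day 0.
- Children withdrawn for medical reasons come under other care: "Participants withdrawn from the study due to medical reasons are referred to adequate health facilities for further care".

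What is left there is an unstated clinical exception that the full protocol may well supply. The screening rule differs because the article itself names the contraindication.

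**Conclusion.** The point holds for the screening rule alone. As written, it directs praziquantel for a child excluded because of a reaction to praziquantel. This is a minor patient-safety correction. The number affected is unknown and probably very small or zero, and sample size, randomisation, analysis and every trial estimate are unaffected. Because the doses concerned were probably complete by publication, the correction serves mainly accurate reporting and re-use of the protocol.

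The conclusion rests on reading the sentence literally and on the article alone; the full protocol may already be worded better. It does not imply that any hypersensitive child was dosed, and the article gives no evidence of that.

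**What to change.** Add an exception to the sentence on ineligible children under Screening, enrollment, and participant follow-up: praziquantel is given unless the child was excluded for praziquantel hypersensitivity, in which case it is withheld and the child is referred for alternative care. If the full protocol already says this, the article need only be brought into line with it.

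The cost is one clause. The history needed is already asked for when the exclusion criterion is applied; the clinician has only to note that praziquantel was the drug concerned. The one downside is that treatment is delayed, through referral, for the rare child held back.

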**Enrollment**							
Stool examination	X						
Eligibility screen	X						
Informed consent/assent		X					
Child assent		X					
Randomization		X					
**Intervention**							
Praziquantel alone			X				
Praziquantel plus ACT^a^			X	X	X		
**Assessment**							
Baseline assessment							
Body weight and height	X					X	X
Hemoglobin (HemoCue)	X					X	X
Outcome assessment							
Stool examination						X	X
Safety assessment							
Adverse events	X		X	X	X	X	

^a^ACT includes any of artesunate plus sulfalene-pyrimethamine, artesunate plus amodiaquine, artesunate plus mefloquine, or dihydroartemisinin-piperaquine

#### Parasitological monitoring of response to treatment

All the laboratory tests are performed by the laboratory at the sub-county hospital, using standard techniques. To assess for the presence of *S. mansoni*, participants provided a fresh stool sample. Duplicate slides are prepared from the stool sample and examined under the microscope independently by two experienced laboratory technicians. The *S. mansoni* and soil-transmitted helminth eggs are quantified by use of the Kato-Katz fecal thick-smear technique, with a template containing about 41.7 mg of feces when filled. The number of *S. mansoni* eggs is counted per slide, and the mean of the two readings is multiplied by 24 to express them as eggs per gram (EPG) of feces. The intensity of infection is categorized according to the WHO classification as light (1–99 EPG), moderate (100–399 EPG), or heavy (≥ 400 EPG) [30]. As a quality control measure for interobserver variability, a third technician reads a random selection of 10% of slides, and all slides for which the initial readings vary by more than 20% between the two technicians.

### Hemoglobin assessment

The study clinician takes a fingerprick blood sample at screening and week 6 and week 12 follow-up visits to determine the hemoglobin level. The hemoglobin level is estimated using a portable hemoglobinometer (HemoCue Hb 301, HemoCue, Angelholm, Sweden). The hemoglobin value obtained is categorized according to the WHO criteria [31].

### Treatment

The participants are allocated individually to treatment groups. The treatments administered in this study are as follows:Praziquantel (PZQ) (Biltricide, Bayer Healthcare, Leverkusen, Germany) is a tablet with 600 mg active ingredient. PZQ is administered as a single oral dose of 40 mg/kg body weight.Artesunate plus sulfamethoxypyrazine/pyrimethamine (AS+SP) (Coarinate Junior, Dafra Pharma, Turnhout, Belgium) is a fixed-dose combination tablet consisting of 100 mg artesunate, 250 mg sulfamethoxypyrazine, and 12.5 mg pyrimethamine. Participants receive a dose of artesunate plus sulfalene/pyrimethamine (4 mg/kg of the artesunate component) tablets once daily for 3 days.Artesunate plus amodiaquine (AS+AQ) (ASAQ, Winthrop, Sanofi-Aventis, France) is a fixed-dose combination tablet consisting of 100 mg artesunate and 270 mg amodiaquine. Participants receive a dose of artesunate plus amodiaquine (4 mg/kg of the artesunate component) tablets once daily for 3 days.Artesunate plus mefloquine (AS+MQ) (ARTEQUIN, Acino/Mepha, Switzerland) is a fixed-dose combination tablet consisting of 200 mg artesunate and 250 mg mefloquine. Participants receive a dose of artesunate plus mefloquine (4 mg/kg of the artesunate and 8.3 mg/kg/day of mefloquine) tablets once daily for 3 days.Dihydroartemisinin-piperaquine (DHAP) (D-ARTEPP, Guilin Pharmaceutical Co. Ltd, China) is a fixed-dose combination tablet containing 40 mg of dihydroartemisinin and 320 mg of piperaquine. Participants receive a dose of dihydroartemisinin-piperaquine (4 mg/kg/day of dihydroartemisinin and 20 mg/kg/day of piperaquine) tablets once daily for 3 days.

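### In two of the four ACT arms, the paired mg/kg doses cannot both be delivered by the fixed-dose tablets named for those arms

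*Protocol article*

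**What the plan says.** The Study design section of the protocol article sets one dosing rule for all four ACT arms: "4 mg/kg of the artemisinin component, once a day for three consecutive days, as fixed-dose WHO-recommended combination treatment".

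The Treatment section then describes each product.

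- **DHAP:** the product "is a fixed-dose combination tablet containing 40 mg of dihydroartemisinin and 320 mg of piperaquine", and the daily dose is "4 mg/kg/day of dihydroartemisinin and 20 mg/kg/day of piperaquine".
- **AS+MQ:** the product "is a fixed-dose combination tablet consisting of 200 mg artesunate and 250 mg mefloquine", and the dose is "4 mg/kg of the artesunate and 8.3 mg/kg/day of mefloquine", given once daily.
- **Artesunate plus sulfalene/pyrimethamine and artesunate plus amodiaquine:** only the artesunate dose is stated, so these entries contain no pair of doses that could conflict.

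The section on screening, enrollment and follow-up adds that a treatment sheet with the regimens is supplied as Additional file 1, Appendix 4 (not shown here). It also says that dosing is directly observed, that the nurse records the dose for each child, and that weight is measured.

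**The concern.** When two drugs are in one tablet, the dose of one fixes the dose of the other. A plan may therefore state two mg/kg doses for a fixed-dose tablet only if their ratio matches the tablet's. In the DHAP and AS+MQ entries it does not, so no child in either arm can receive both stated doses from the stated tablet.

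Three things are at stake.

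1. **Safety.** Drug-related adverse events in the first 24 hours after treatment are listed among the primary outcomes, in children aged 9 to 15. Their frequency in these two arms is hard to interpret if the partner-drug dose is uncertain by this much. The article also gives the drugs' established safety profile as part of the reason for having no data safety monitoring board, and such a profile belongs to a particular dose.
2. **Comparison between ACTs.** The article presents the head-to-head comparison as the trial's strength, and the Study design section gives all four ACT arms the same artemisinin dose. If the partner-drug figures governed dosing, that statement would not hold for these two arms.
3. **Reproducibility.** A reader of the article cannot tell which regimen a result for these arms would support.

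**Working it through.** **Inputs, all from the Treatment section**

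| Arm | Tablet (artemisinin / partner) | Stated daily dose (artemisinin / partner) |
|---|---|---|
| DHAP | 40 mg / 320 mg | 4 mg/kg / 20 mg/kg |
| AS+MQ | 200 mg / 250 mg | 4 mg/kg / 8.3 mg/kg |

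**Formula.** A child of weight *w* kg who takes *n* tablets a day receives *n* × (artemisinin mg per tablet) / *w* of one drug and *n* × (partner mg per tablet) / *w* of the other. Both *n* and *w* cancel in the ratio. Hence:

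- partner dose = artemisinin dose × (partner mg / artemisinin mg per tablet)
- artemisinin dose = partner dose × (artemisinin mg / partner mg per tablet)

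**Step 1: can the stated pairs be reproduced?**

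- DHAP: tablet ratio 320/40 = 8; dose ratio 20/4 = 5. They do not match.
- AS+MQ: tablet ratio 250/200 = 1.25; dose ratio 8.3/4 = 2.075. They do not match.

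**Step 2: what the tablet delivers if one stated dose is met**

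| Arm | Dose met | Other drug delivered | Against the stated figure |
|---|---|---|---|
| DHAP | dihydroartemisinin 4 mg/kg | piperaquine 4 × 8 = 32 mg/kg | 32/20 = 1.60, 60% above |
| DHAP | piperaquine 20 mg/kg | dihydroartemisinin 20/8 = 2.5 mg/kg | 2.5/4 = 0.625, 37.5% below |
| AS+MQ | artesunate 4 mg/kg | mefloquine 4 × 1.25 = 5 mg/kg | 5/8.3 = 0.60, 40% below |
| AS+MQ | mefloquine 8.3 mg/kg | artesunate 8.3/1.25 = 6.64 mg/kg | 6.64/4 = 1.66, 66% above |

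**Step 3: in tablets, for an assumed child of 40 kg** (the eligibility limit is below 50 kg)

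- DHAP by dihydroartemisinin: 4 × 40 / 40 = 4 tablets a day, which contain 4 × 320 = 1280 mg piperaquine.
- DHAP by piperaquine: 20 × 40 / 320 = 2.5 tablets a day, which contain 2.5 × 320 = 800 mg piperaquine.
- AS+MQ by artesunate: 4 × 40 / 200 = 0.8 tablets a day.
- AS+MQ by mefloquine: 8.3 × 40 / 250 = 1.33 tablets a day.

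**Step 4: can a convention explain it?** Weight bands, split tablets and rounding change *n*, not the ratio. Averaging over children does not help either, because the ratio of the mean doses is still the tablet ratio. A single convention such as salt versus base would not explain both arms, since the stated partner dose is below what the tablet gives in DHAP and above it in AS+MQ. The text states no such convention.

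**Step 5: bound on the common artemisinin dose.** If both arms were dosed by the partner drug, the artemisinin dose would be 2.5 mg/kg in DHAP and 6.64 mg/kg in AS+MQ, a ratio of 6.64/2.5 = 2.66. This is a hypothetical extreme.

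**The case against.** The strongest reply is that the article is not the dosing instruction. Appendix 4 holds the treatment sheet, it is not shown here, and it may fix exactly how many tablets each child received. Dosing was directly observed and the dose recorded for each child. A reader might infer from the mismatch that the regimen was never defined, or that results in these arms can never be tied to a known dose. The documents do not support either inference: the sheet may define the regimen, and the records together with the measured weights should allow the delivered dose to be recovered. What remains is that no sheet can make both mg/kg figures true for these tablets. Nor is this an omission of the kind a condensed article is allowed, because the article states specific figures that exclude each other.

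A second reply is that the main comparison does not need equal artemisinin doses. That is correct. The Outcomes section compares each combination arm with praziquantel alone, and the non-inferiority test follows it. A reader might infer that the trial's comparisons as a whole rest on the common 4 mg/kg. They do not; the point touches only contrasts between ACT arms, which the article advertises but does not make its primary hypothesis.

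A third reply is that the Study design section expresses ACT dosing by the artemisinin component, so nothing shown says that either arm was dosed by the partner drug. This also stands, and the 2.5 versus 6.64 mg/kg contrast should be read only as a bound.

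Finally, one strength or dose in each entry may simply be misprinted. That is possible, but only the records can show it, and two arms are affected.

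**Conclusion.** The contradiction is established from the article's own figures and needs no outside source. In the DHAP and AS+MQ arms the stated tablet cannot deliver the stated pair of doses. Depending on which component is met, the other misses its stated value by 37.5% to 66%, which is too much to be rounding. The regimen in these two arms therefore cannot be determined from this text. The statement of "4 mg/kg of the artemisinin component, once a day for three consecutive days" fits these arms only if the printed partner-drug doses were not the ones followed.

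The consequence is mainly for interpreting the primary safety endpoint and for any comparison among the ACTs. The non-inferiority comparison with praziquantel alone remains a valid comparison of the arms as treated, but its result in these arms needs a delivered dose attached.

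The conclusion assumes that the tablet strengths are as printed, that both mg/kg figures are daily doses, and that each was meant to be given from the named tablet alone. It takes no view on which figure is right.

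**What to change.** 1. Reconcile the tablet strengths and mg/kg doses in the Treatment section, and the common artemisinin dose in Study design, with Appendix 4 and the dose recorded for each child. Which figure is right is for the sponsor's clinical team.
2. Correct the article text so that tablet strength, both component doses and the Study design statement agree.
3. Compute delivered mg/kg of both components for each child (tablets given × strength / weight), and report it by arm with the efficacy and safety results.
4. Qualify the statement of a common artemisinin dose if it proves not to hold in these arms.
5. Check the approved protocol (version 1.2), and notify the ethics committee if the same conflict appears there. If it exists only in the article, a published correction is enough.

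The cost is small. Recruitment closed on 30 November 2022 and treatment lasts three days, so dosing is complete. The work is a check of existing records, one descriptive table and a text correction. Randomization, sample size and the primary test are unaffected.
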